## Abstract

**Introduction:**

Assessment of renal tissue and renal tumor stiffness may provide complementary information for tissue characterization; however, conventional imaging modalities such as multiphasic computed tomography (CT) do not directly quantify biomechanical properties. Elastography techniques, including magnetic resonance elastography (MRE) and ultrasound elastography (US-E), allow noninvasive measurement of tissue stiffness but are not routinely available in standard clinical practice. This study protocol aims to develop a CT-based stiffness mapping of renal parenchyma and renal tumors by investigating the relationship between CT attenuation values and elastography-derived stiffness measurements, using MRE and US-E as reference modalities.

**Methods and analysis:**

This monocentric, prospective, exploratory, non-randomized, and non-blinded diagnostic study will enroll 50 adults undergoing partial or radical nephrectomy for renal tumors at the University Hospital of Bordeaux. All participants will undergo a predefined multimodal imaging protocol—including contrast-enhanced CT, multiparametric magnetic resonance imaging (MRI) with -MRE and US-E—conducted between inclusion and the day before surgery. The primary objective is to construct a regression model predicting MRE-derived elasticity (μMRE) from CT density values using multiple machine-learning algorithms evaluated through repeated nested cross-validation. Secondary analyses will include voxel-level and region-of-interest correlations across modalities, feasibility and image-quality assessment of DWI-vMRE, repeatability of elastography measurements, identification of limiting factors such as BMI, sarcopenia, lesion location and architecture, evaluation of inter-modality de-correlation and associations with final histopathology (including subtype and grade).

**Trial registration:**

ClinicalTrials.gov identifier: NCT06525831. Protocol ID-RCB: 2024-A00959-38. Recruitment began on 7 March 2025.

## Introduction

Renal cell carcinoma (RCC) accounts for approximately 3–5% of all adult malignancies and represents the seventh leading cause of cancer-related mortality in men and the tenth in women [1]. More than 50% of RCCs are discovered incidentally during imaging performed for unrelated purposes [2]. Medical imaging plays a central role in the diagnostic and therapeutic management of RCC. It enables confirmation and localization of renal lesions, assessment of malignancy and histological subtype, TNM staging, surgical planning, biopsy guidance, treatment monitoring, and detection of recurrence. Ultrasound (US), CT and magnetic resonance imaging (MRI) are complementary modalities in this setting, with CT widely used for three-dimensional reconstruction and preoperative modeling. However, the relationships among renal tissue density on multiphasic CT, enhancement characteristics, and tissue stiffness measured through US and MRI remain insufficiently defined. Accurate estimation of renal tissue stiffness from imaging could expand the diagnostic capabilities of CT and improve the anatomical and mechanical fidelity of 3D models used for surgical planning. Multiparametric magnetic resonance imaging (mpMRI) is currently the most advanced imaging modality for renal tumor characterization and for differentiating histological subtypes. However, its diagnostic performance remains insufficient to reliably obviate invasive biopsy procedures when tumor malignancy is not clearly

A meta-analysis including 1,239 solid renal lesions reported an overall correct classification rate of 64%, with sensitivity of 95% and specificity of 63% [3]. In another multicenter prospective study of 250 small renal masses (<4 cm), mpMRI yielded a sensitivity and specificity of 75% and 79%, respectively, for diagnosing clear cell RCC (ccRCC), with modest interobserver agreement (κ = 0.58) [4]. As a result, approximately 30% of partial or radical nephrectomies are performed for benign lesions—most commonly fat-poor angiomyolipomas and oncocytomas—leading to avoidable morbidity, including hemorrhage, fistula, and infection in about 16% of cases [2,5]. mpMRI provides the most comprehensive integration of morphological and functional parameters for renal tumor characterization. By combining T1- and T2-weighted sequences, chemical-shift imaging, dynamic contrast-enhanced imaging, and diffusion-weighted imaging, mpMRI offers richer insights into tumor phenotype compared with CT [3]. However, even with machine-learning–based predictive models, diagnostic reproducibility and clinical reliability remain suboptimal [3,6–8]. Beyond morphological evaluation, MRI allows quantitative assessment of biomechanical properties through MRE. Preliminary studies have shown strong correlations between renal parenchymal stiffness and histopathological features such as tubulo-interstitial fibrosis, extracellular matrix expansion, and glomerulosclerosis [9,10], as well as associations between intratumoral elasticity and certain histological subtypes [11]. Prezzi et al. included 18 patients with renal tumors measuring 2–5 cm. MRE demonstrated superior discrimination between histological subtypes compared with other individual MRI sequences, including T2-weighted imaging, diffusion-weighted imaging, and dynamic contrast-enhanced imaging, particularly in differentiating clear cell RCC from oncocytoma (p = 0.007) These findings support the emerging diagnostic value of biomechanical imaging biomarkers. CT remains the reference modality for anatomical segmentation and 3D model construction because of its robustness and accessibility; however, no established relationship currently exists between CT density values and tissue stiffness derived from elastography. Establishing these correlations could enhance CT predictive value and improve the realism of 3D-printed kidney models [12–15].

## Materials and methods

### Aim

The following protocol tries to evaluate the concordance of advanced imaging techniques in assessing renal tissue stiffness for preoperative evaluation of renal tumors in patients undergoing a partial or radical nephrectomy for renal tumor at the Centre Hospitalier Universitaire Bordeaux. This protocol includes multiphasic CT, MRE and US-E, performed between inclusion and the day before surgery.

### Trial

This is a monocentric, prospective, explorator, non-randomized, and non-blinded diagnostic study. Patients enrolled are prospectively followed from inclusion to surgery, with all imaging procedures performed within a predefined preoperative window. All participants undergo a predefined multimodal imaging workflow including multiple diagnostic modalities, incorporing contrast-enhanced CT, mpMRI (including MRE) and US-E, aiming to explore the diagnostic potential of these techniques in the characterization of renal tumors and renal-parenchyma.

### Ethic declarations

The protocol number is ID-RCB 2024-A00959-38, version 2.0 from 16/10/2025. The study received regulatory approval from the Comité de Protection des Personnes (CPP) ÎdF1 and authorization from the ANSM. Patient recruitment began on 7 March 2025, and enrolment is planned over an 18-month period, followed by a 4-month completion phase for final assessments.The trial is registered on ClinicalTrials.gov with the reference NCT06525831 (Study Details | NCT06525831 | Rein 3D PRINT MECHANICS | ClinicalTrials.gov). All study procedures are conducted before surgery at the University Hospital of Bordeaux.

In accordance with French Law No. 2002-303 of March 4, 2002, participants were informed of their right to access the overall results of the study upon request.

### Study population

The study will enroll 50 patients with renal tumors referred for surgical management at the University Hospital of Bordeaux. Patients eligible for inclusion must be at least 18 years old or older, scheduled for nephrectomy for renal neoplasm within the Urology Department, and have a planned or available multiphasic CT as part of their preoperative workup. Participants must also provide informed consent for inclusion in the UroCCR cohort and participation in the Rein-3D Print Mechanics study, with the condition that they are affiliated with social security system. Exclusion criteria include pregnancy or breastfeeding, contraindications to MRI or gadolinium-based contrast agents, previous renal biopsy <15 days before MRI, and certain comorbidities such as obesity (body mass index (BMI) ≥ 30 kg/m²), thoracolumbar spinal fixation, or the presence of small (<2 cm) cystic or necrotic renal tumors with a solid component. Additionally, patients with ascites, legal protection measures, or difficulty in understanding and expressing themselves in French will be excluded.

All study data will be recorded in the imaging systems (Carestream PACS; Philips) and UroCCR database, managed by the CREDIM (Centre de Recherche et Développement en Informatique Médicale) at the University Hospital of Bordeaux. The database is authorized by the French Data Protection Authority (CNIL; authorization DR-2013–206, request n°912578) and operates under the national MR-001. The study involves senior urologists, expertised radiologists from the uro-vascular imaging department, the reference pathologist, biomedical engineers, data managers and biostatisticians.

Data entry was performed by trained personnel, and clinical variables were coded using standard dictionaries (MedDRA, ATC). Data quality was ensured through automated checks and query resolution. All data were pseudonymized, securely stored, and transferred via a protected platform when required. Confidentiality was maintained in accordance with regulatory standards, and study data were archived for 20 years.

### Study setting

This study aims to investigate the relationships between renal tumor biomechanical properties measured by multimodal imaging and underlying tumor characteristics, with the broader objective of improving non‑invasive diagnostic approaches. The study will enroll 50 patients scheduled for nephrectomy over an 18‑month period, with follow‑up extending 4 months after inclusion. To date, 40 patients have been enrolled, and recruitment is expected to be completed by September 2026. Approximately 250 patients per year are referred to the Department of Urology for the initial evaluation of renal lesions, establishing a robust recruitment base that is further strengthened by their established clinical and research collaborations through multidisciplinary tumor board meetings. Eligible patients will be recruited during urology consultations at Pellegrin Hospital or after identification by radiologists during imaging sessions. All participants will provide written informed consent in accordance with the approved protocol. Preoperative imaging will include ultrasound elastography, mpMRI (including MRE), and contrast‑enhanced CT, all performed within a standardized preoperative window to ensure methodological consistency. These imaging procedures will take place at Saint‑André Hospital for MRI and at Pellegrin Hospital for ultrasound examinations, using standardized equipment and performed by senior radiologists, with routine care multiphasic CT incorporated as clinically indicated. After the nephrectomy pathological analyses will follow standard institutional workflows. Imaging data will be analyzed at the voxel level for MRI and CT, and at the region of interest (ROI) level for US-E. All data will be managed securely according to protocol specifications until completion following the availability of the final histopathological report.

### Procedure

Each patient meeting the eligibility criteria will be enrolled during a dedicated inclusion visit (T0). During this visit, the investigator provides complete study information, verifies all inclusion and exclusion criteria, and obtains written informed consent before any research-related procedure is performed. Women of childbearing potential undergo a urine pregnancy test; a positive result leads to exclusion. As part of routine care, a contrast-enhanced multiphasic -CT will be performed if not already available at inclusion.

Between inclusion and surgery, all imaging examinations related to the study (T1) will be carried out by skilled radiologists and all ultrasound examinations will be performed on the same ultrasound machine to ensure consistency. mpMRI will be conducted at the Saint-André imaging department, on a different day than the CT, following standard clinical practice due to the use of contrast agents. The MRI examination lasts approximately 30–40 minutes and uses the routine gadolinium-based contrast agents DOTAREM® or CLARISCAN® at the recommended dose (0.1 mmol/kg). CT and MRI will ideally be scheduled within 15 days of each other, with a maximum allowed interval of 28 days to minimize the risk of tumor evolution between exams. Ultrasound elastography will be performed at Pellegrin Hospital, potentially during the same visit as the planning CT, and lasts approximately 15 minutes.

The T2 visit corresponds to the scheduled nephrectomy performed as part of routine care.

No additional follow-up visits are planned. Study participation ends when the results of the routine histopathological examination become available, up to one month after surgery. The last research-related procedure corresponds to the final imaging examination (ultrasound or MRI), and at the latest the day before surgery. Subsequent clinical care is conducted according to standard practice (Figs 1 and 2).

**Fig 1 pone.0351477.g001:**
[figure not shown]
MECHANICS Protocole participant timeline.

**Fig 2 pone.0351477.g002:**
[figure not shown]
Study workflow.

### Outcome measures

The primary outcome of this study is to develop a predictive model of biomechanical properties of both normal and pathological renal tissue, using MRE as the reference, based on density values from multiphasic CT. All analyses will be conducted before the definitive histological diagnosis.

The secondary outcomes are:

Multimodal correlation: to correlate elasticity values obtained by MRE, and ultrasound elastography with CT density values, on a voxel to voxel, ROI to ROI, and anatomical region basis across all CT acquisition phases.Feasibility of DWI-vMRE: This study aims to assess the feasibility and optimization of parameters for DWI-vMRE using a clinical 1.5-Tesla MRI scanner. It will focus on evaluating key performance metrics, including image quality (qualitative assessment), contrast-to-noise ratio (CNR), signal-to-noise ratio (SNR), and the identification and documentation of artifacts.Feasibility of elastography modalities: to assess the feasibility of MRE, and US–E for quantifying renal parenchymal and tumoral stiffness, and to identify limiting factors (e.g., BMI, sarcopenia, lesion location, size, and architecture), including enumeration of non-diagnostic examinations.Repeatability analysis: to evaluate the repeatability of MRE, and US-E across the cohort and within subgroups defined by patient morphotype and tumor characteristics, using intraclass correlation coefficients and Bland–Altman plots.De-correlation and bias analysis: to identify situations of de-correlation or potential biases between biomechanical measurements obtained from MRE and US-E (e.g., extreme elasticity values, morphotype-related limitations).Histopathological associations: to assess associations between biomechanical properties (measured or CT-predicted) and final histological subtype; and, for clear cell renal cell carcinoma, with histological grade. This includes ROC curve analyses and identification of potential diagnostic cutoff values.

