### Imaging analysis workflow

CT and MRI datasets will be anonymized and transferred to a dedicated research workstation for postprocessing. Tumor and renal parenchyma segmentations will be performed semi-automatically by an imaging engineer and a radiologist with expertise in genitourinary imaging, blinded to histopathological results and elastography measurements. Segmentations will include the whole tumor volume on axial images. An in-board software (Sophia DDM for Radiomics, SophiaGenetics SA, Saint-Sulpice, Switzerland) was used.

For renal parenchyma analyses, cortical and medullary ROIs will be separately defined on anatomically matched slices.

Multimodal image co-registration between CT and MRI datasets will be performed using rigid registration followed, when necessary, by deformable registration to compensate for respiratory and positional differences. All images will be resampled to a common voxel resolution before voxel-wise analysis.

Quality control procedures will include visual assessment of registration accuracy and exclusion of non-diagnostic datasets.

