### Statistical analysis

Imaging data will be acquired across multiple modalities, including MRE (μMRE), US-E, and CT (dCT, dCT40s, dCT90s, dCT10min), alongside clinical and morphological variables such as BMI, sarcopenia, lesion size, volume, location, histological type, malignancy status, and histological grade for clear cell renal carcinoma, where applicable. Quantitative variables will be extracted and analyzed for each region of interest (ROI). Descriptive statistics will summarize categorical variables as frequencies and percentages, while continuous variables will be presented as mean, standard deviation, median, range, and interquartile range.

The primary objective is to develop a regression model to predict μMRE based on CT-derived density values. The dataset will be divided into a 70% training set and a 30% test set, and various regression algorithms (linear regression, elastic net, k-nearest neighbors, support vector machines, random forests, and artificial neural networks) will be compared using repeated nested cross-validation. Model performance will be evaluated based on coefficient of determination (R²), mean squared error (MSE), and root mean squared error (RMSE), with RMSE serving as the primary criterion for model selection. Reproducibility of MRE measurements will be assessed through repeated acquisitions, with the highest-quality sequence selected for model development.

Secondary analyses will investigate the interrelationships between biomechanical parameters across imaging modalities. Spearman’s rank correlation coefficient will be used to assess correlations between elasticity values from MRE, US-E, and CT densities. The feasibility and image quality of DWI will be evaluated using a five-point qualitative scale, contrast-to-noise ratio, signal-to-noise ratio, and systematic reporting of artifacts. Non-diagnostic examinations and potential limiting factors—such as patient morphotype, sarcopenia, and lesion characteristics—will be documented. The repeatability of elastography measurements will be quantified using intraclass correlation coefficients and Bland-Altman plots. Cases of modality de-correlation will be explored through paired scatterplots and descriptive analysis of discordant data points.

The final statistical analysis plan will be reviewed and approved by the Scientific Committee prior to database lock.

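### If normal and tumour tissue are scored together, a good overall R² for the CT model may reflect recognition of tissue type rather than stiffness information within a tissue

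*Protocol article*

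**What the plan says.** The Abstract (Introduction) gives the aim as to "develop a CT-based stiffness mapping of renal parenchyma and renal tumors". Outcome measures makes the primary outcome to "develop a predictive model of biomechanical properties of both normal and pathological renal tissue", with MRE as the reference. Statistical analysis repeats this in the singular: "The primary objective is to develop a regression model to predict μMRE based on CT-derived density values". The CT densities listed there are dCT, dCT40s, dCT90s and dCT10min. Performance is measured by R², MSE and RMSE, "with RMSE serving as the primary criterion for model selection".

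Imaging analysis workflow has the whole tumour segmented, and for parenchyma "cortical and medullary ROIs will be separately defined on anatomically matched slices". The tissue of each measurement is therefore known. The description of the primary analysis does not use it: it fixes target, predictors, metrics and selection criterion without a tissue term, a score per tissue or a reference model.

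Among the secondary outcomes, correlations of MRE and ultrasound elastography with CT density are planned "on a voxel to voxel, ROI to ROI, and anatomical region basis across all CT acquisition phases".

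**The concern.** Cortex, medulla and tumour can differ in enhancement across CT phases and may differ in mean stiffness. A model fitted across all three can then reduce its error by working out which tissue it is looking at and returning that tissue's typical stiffness. The segmentation already supplies the tissue, so such a model adds nothing to it, and its stiffness map is the segmentation recoloured.

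What is at stake is the reading of the primary result. Stiffness mapping, and the secondary analyses relating CT-predicted properties to histological subtype and to grade in clear cell carcinoma, need information within a tissue. An overall R² does not show whether it is there. Nor does the overall RMSE, unless it is set beside the within-tissue spread.

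**Working it through.** The article gives no target R² or RMSE and no tissue means or SDs, so there is no figure of its own to reproduce. All spacings below are assumptions, in units of the within-tissue SD. From the article come the 50 patients, the 70/30 split, the three tissues and the four CT densities. A split by patient (0.7 × 50 = 35 and 0.3 × 50 = 15) and one value per tissue per patient are assumed.

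**1. Ceiling.** Let mean stiffness be −d, 0, +d in three equally weighted tissues, with within-tissue variance 1 and no within-tissue link to CT. The between-tissue variance is 2d²/3. If CT identifies the tissue perfectly,

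R² = (2d²/3) / (1 + 2d²/3).

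For d = 1: 0.667/1.667 = 0.40. RMSE falls only to the within-tissue SD, which is √(1 − 0.40) = 0.77 of the total SD. If only tumour differs by d, the between-tissue variance is 2d²/9, and d = 1 gives 0.222/1.222 = 0.18.

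**2. One density, linear model.** Let HU means be −2, 0, +2 within-tissue SD, ranked as stiffness is. The covariance is 4d/3 and the HU variance is 1 + 8/3, so

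R² = (4d/3)² / [(1 + 8/3)(1 + 2d²/3)].

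- d = 0.5: 0.444/4.278 = 0.10
- d = 1.0: 1.778/6.111 = 0.29
- d = 1.5: 4.000/9.167 = 0.44

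On held-out patients (35/15) simulation gives about 0.08, 0.27 and 0.43, with negative mean within-tissue R².

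The rank order matters. If two neighbouring tissues swap places on stiffness, the covariance halves to 2d/3 and R² falls to a quarter: 0.03, 0.07 and 0.11. Held out, it is about 0.09 or less.

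**3. Four phases, held out.** Assumed mean HU (unenhanced, 40 s, 90 s, 10 min) is 35/160/180/110 for cortex, 32/80/170/115 for medulla and 35/110/110/75 for tumour, with a within-tissue HU SD of 15 or 30. Mean stiffness is −d, 0 and +d in that order, with no within-tissue association. The models are linear regression and k-nearest neighbours (k = 15), with 500 replicates per scenario. Ranges of median test-set R² over both models and both SDs:

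| Spacing d | Ceiling | Overall R² | R² within a tissue |
|---|---|---|---|
| 0 | 0 | −0.09 to −0.06 | −0.13 to −0.08 |
| 0.5 | 0.14 | 0.02 to 0.07 | −0.20 to −0.12 |
| 1.0 | 0.40 | 0.21 to 0.35 | −0.45 to −0.13 |
| 1.5 | 0.60 | 0.34 to 0.56 | −0.85 to −0.14 |
| 2.0 | 0.73 | 0.42 to 0.69 | −1.51 to −0.17 |

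Scoring per tissue exposes the artefact in every row where the overall R² is positive.

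**4. Which benchmark is fair.** Suppose CT does carry signal, with a within-tissue correlation of 0.4, HU means 1 SD apart and stiffness means 1.5 SD apart. A linear model on CT alone has held-out RMSE 1.15, against 1.01 for the tissue mean, and wins in only about 15% of replicates. Label plus CT beats label alone in 91%. The informative contrast is therefore label against label plus CT.

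**The case against.** The strongest reply is that pooling is inferred. The article never says that the tissues are scored by one figure. It says that variables are extracted and analysed per region of interest, and it leaves a final analysis plan to be approved before database lock. A reader might infer that the article commits to a pooled score; it does not, and the point is conditional on the natural reading of a single model for normal and pathological tissue. It nevertheless goes beyond missing detail, because the target, metrics and selection criterion are fixed and, followed as written, allow this result.

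A reader might also infer that the secondary Spearman correlations are confounded in the same way. The text does not support that, since an anatomical-region analysis is already planned. Likewise, the associations with subtype and grade are analyses of tumours, where telling tumour from parenchyma earns nothing. These analyses could reveal a missing within-tissue link, but they do not score the primary model.

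It is also fair to say that the sizes rest on assumed spacings, profiles and rank order, and that no R² or RMSE threshold defines success in this exploratory study. That rules out a fixed estimate of inflation and a formal gate. It does not remove the ambiguity in the headline R².

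**Conclusion.** The point holds conditionally. If tissues are scored together, the overall R² cannot by itself distinguish a CT model that predicts stiffness from one that recognises tissue. With no within-tissue association, the artefact is small at a spacing of 0.5 SD (held-out R² about 0.1 or less) and material from about 1 SD (about 0.2 to 0.35). These figures assume equal tissue weights, a split by patient, and either the four-phase profiles above or a single density with tissues ranked alike on HU and stiffness. Under a swapped order, a linear single-density model shows little of it.

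Two stronger conclusions are not supported. Nothing in the article shows that CT lacks within-tissue information; that is unknown. Nor is RMSE inflated as R² is: it stops at the within-tissue SD, and the difficulty is only that this value is not recognisable without a reference. The change is worth making because it is cheap and bears on the primary claim.

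**What to change.** In the primary analysis, report held-out RMSE and R² separately for tumour, cortex and medulla, using the existing segmentations. On held-out patients, compare a model with the tissue label alone against one with the label plus CT densities, and give the difference in RMSE with a patient-level bootstrap confidence interval. Interpret the result as within-tissue stiffness mapping only to the extent that CT improves on the label. Set no pass/fail rule, as the study is exploratory. Do not set CT alone against a tissue-mean benchmark as the deciding comparison, because only the benchmark would be given the label.

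The cost is a few extra analyses and a headline R² that may look less favourable. No new data are needed, and the final analysis plan is still to be approved before database lock.

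### An association of CT-predicted stiffness with histology cannot by itself show that stiffness is diagnostic, because the prediction is computed from CT densities alone

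*Protocol article*

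**What the plan says.** All references are to the Protocol article.

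- **Outcome measures** sets the histopathology outcome: "to assess associations between biomechanical properties (measured or CT-predicted) and final histological subtype", and histological grade within clear cell carcinoma. It adds: "This includes ROC curve analyses and identification of potential diagnostic cutoff values". Measured and CT-predicted stiffness thus stand side by side as biomechanical properties.
- **Statistical analysis** defines the prediction: "The primary objective is to develop a regression model to predict μMRE based on CT-derived density values". The abstract agrees: "predicting MRE-derived elasticity (μMRE) from CT density values using multiple machine-learning algorithms". The densities listed are "CT (dCT, dCT40s, dCT90s, dCT10min", four in all. BMI, sarcopenia, lesion size and histology are listed as recorded variables and are not named as predictors.
- **Introduction** gives the motive: "Accurate estimation of renal tissue stiffness from imaging could expand the diagnostic capabilities of CT" and, later, "Establishing these correlations could enhance CT predictive value and improve the realism of 3D-printed kidney models".
- Apart from the primary model, the stated use of raw CT densities is correlation with elasticity (Outcome measures; Statistical analysis). No section relates them to subtype or grade.

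**The concern.** Once the model is trained, predicted stiffness is a fixed function of a patient's CT densities. If subtypes enhance differently, the prediction can separate them even where their true stiffness is the same. Calling the result a biomechanical association, and deriving cutoffs on a stiffness scale, invites a conclusion about tissue mechanics that the comparison cannot support.

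The risk is greater because, under Outcome measures, the model covers both normal and pathological tissue. The density-stiffness slope may then come largely from the contrast between parenchyma and tumour, and still be applied to differences between tumours.

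What is at stake is the interpretation of one secondary outcome. The Introduction hopes that stiffness will extend what CT can diagnose, and the CT-predicted half of this outcome cannot show that without a reference to the densities themselves.

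**Working it through.** The article gives no alpha, power or effect size for this outcome, so there is no figure to reproduce. The check is structural, with two illustrations. Every simulation input is an assumption, and none comes from the article except the total of 50 patients and the four densities.

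**Step 1, structure.** Let d = (d1, d2, d3, d4) be the four densities and Ŝ = f(d) the prediction, with f fixed after training. For a new patient, once d is known, Ŝ adds nothing about histology. In the population, AUC(Ŝ) ≤ AUC of the best classifier built on d. In the linear case, the design matrix [1, d] has rank 5, and [1, d, Ŝ] also has rank 5, so Ŝ has no coefficient of its own. For nonlinear algorithms Ŝ is still a transform of the same inputs.

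The restriction to patients outside the training data matters. A flexible learner, such as nearest neighbours or a random forest, can carry a training patient's own μMRE into that patient's prediction.

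**Step 2, stiffness unrelated to subtype.** Assumptions: 35 versus 15 patients; one CT phase differing by 1.2 SD between subtypes; tumour stiffness unrelated to subtype and density; slope driven by parenchyma; linear fit on 50 tumour and 50 parenchyma ROIs.

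- Analytic AUC of the density: Φ(1.2/√2) = Φ(0.849) = 0.802.
- Simulation, 2,000 runs, mean R² 0.20:

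| Marker | Mean AUC |
|---|---|
| Measured stiffness | 0.501 |
| CT-predicted stiffness | 0.803 |
| Raw density | 0.803 |

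With one density and a positive linear slope, the prediction is a rescaling of the density, so the last two rows agree by construction.

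**Step 3, four densities.** Assumptions: pairwise correlation 0.5; R² of stiffness on densities 0.40; binary histology; 200,000 records, half for fitting and half for testing. In scenario A stiffness adds nothing beyond the densities. In scenario B it does.

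| AUC | A | B |
|---|---|---|
| CT-predicted stiffness | 0.687 | 0.663 |
| Raw densities | 0.727 | 0.698 |
| Densities plus measured stiffness | 0.727 | 0.797 |

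The gain from measured stiffness is 0.727 − 0.727 = 0.000 in A and 0.797 − 0.698 = 0.099 in B. In 2,000 samples of 50 patients, CT-predicted stiffness was associated with histology at p < 0.05 in 64% under A and 50% under B. A positive result for the prediction therefore does not tell the two situations apart.

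**The case against.** Several points on the other side stand.

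- **The outcome claims only associations.** The added-value idea comes from conditional sentences in the Introduction, and more realistic 3D models are a separate motive. A reader might infer that the plan promises incremental diagnostic value from predicted stiffness. It does not.
- **The analysis plan is not shown.** Comparators for a secondary ROC analysis are often left to it, and the Statistical analysis section describes no histology analysis. A reader might infer that no raw-density comparator is planned. The article supports only that none is named in it.
- **Measured stiffness is already listed.** That analysis is not circular. If both markers are reported, a discordance such as 0.50 against 0.80 would be visible. A reader might infer that the whole histology outcome is uninformative, and that would be wrong.
- **The illustrations follow from their inputs.** The assumption in Step 2 that stiffness is unrelated to subtype runs against the 18-patient study cited in the Introduction, where MRE separated clear cell carcinoma from oncocytoma (p = 0.007).
- **A score trained on stiffness may be a useful reduction of four densities to one marker.** With 50 patients it could even outperform an overfitted density model. That would be a gain in efficiency, not new information, and showing it also needs the density comparator.

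These points limit the size of the finding but leave its core. The article itself places CT-predicted stiffness beside measured stiffness as a biomechanical property, and that wording governs how the result will be read.

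**Conclusion.** The point holds in a limited form. Because the article names CT densities as the only inputs to the prediction, an association of CT-predicted stiffness with subtype or grade is not, by itself, evidence that stiffness is diagnostic or adds to CT. This rests on two conditions: that no predictor other than CT density enters the model, and that predictions are made for patients outside the training data.

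No size of bias can be given for this trial. The AUCs above show what can happen under assumed inputs. The primary outcome and the measured-stiffness analysis are unaffected. This is one secondary outcome of an exploratory study, so the matter is moderate. It still deserves a change, because the remedy is nearly free and alters what may be concluded.

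**What to change.** 1. In the histopathology outcome, report the AUC of the raw phase densities beside those of CT-predicted and measured stiffness, in the same patients. Use out-of-fold predictions, so that no patient's own μMRE enters that patient's predicted value.
2. Describe CT-predicted stiffness as a transformed CT marker. State that its association with subtype or grade will not be interpreted as a stiffness effect unless measured μMRE shows it too.
3. Optionally, and as exploratory only, report with a confidence interval the gain in AUC from adding measured μMRE to the densities. State that precision will be low: there are 50 patients spread over several subtypes, and the grade analysis uses only the clear cell cases.

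The data are already to be collected and no procedure is added. According to the Statistical analysis section, the final analysis plan is still to be approved before database lock, so the wording can go there. The cost is a little more analysis, and the claim for CT-predicted stiffness may become less favourable.
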